#### 2.8.2. Analysis by Protocol

Only those volunteers who have completed more than 85% of the training sessions will be considered for this analysis. The same procedures as those indicated for intention-to-treat analysis will be conducted.

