## 1. Introduction

Scientific evidence has extensively documented the benefits of regular physical activity on various health variables in older people [1,2,3,4,5]. For example, a significant reduction in resting blood pressure and heart rate [4], lower incidence of cardiovascular events [6] and falls [1,2], a significant increase in cardiorespiratory fitness, muscular endurance and strength, flexibility, agility, and dynamic balance [7,8], as well as significant improvements in attention [9] and cognitive processing speed [10]. Facts that, as a whole, favor functional independence and improve health-related quality of life in older people [3,4].

Some of the most recurrent physical activity strategies to intervene in older people correspond to resistance training [1,5], multi-component training [7,11], and walking exercise [6,12], probably because they have greater diffusion, scientific support, and versatility to dose the magnitude of the load and the exercises to the characteristics of the participants [5,13]. Following the above, government-sponsored physical activity programs for older people have reported endurance, strength, flexibility, balance, agility, walking, healthy dancing, and recreational sports as the main activities. However, their average adherence rate reaches 50% [4].

In the same context, physical activity interventions for older people based on Olympic combat sports have reported a mean adherence greater than 80% [8,13,14], with similar physical, physiological, and psychoemotional outcomes to other physical activity intervention strategies such as those mentioned above (resistance training, multi-component training, and walking exercise). Specifically, interventions with adapted taekwondo in older people have reported a significant increase in muscle strength of the lower [9,15] and upper limbs [15], cardiorespiratory fitness [9], flexibility [9], agility and dynamic balance [9,15,16,17], as well as significant improvements in the multidirectional reach test and a significant decrease in the gait stability ratio [17]. Cho and Roh [9] reported a significant increase in brain-derived neurotrophic factor, vascular endothelial growth factor, and insulin-like growth factor-1, while Lee, Scott, Pekas, Lee, Lee and Park [15] reported a significant decrease in resting epinephrine. In summary, taekwondo improves the health status of older people with adherence rates greater than 90% through interventions lasting 11 to 16 weeks [9,15,16,17].

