### 2.5. Participants

The participants will be recruited in the city of Talca (Maule region), Chile. The inclusion criteria for the sample will be: (i) older women aged between 60 and 65 years old; (ii) presenting the ability to understand and follow instructions in a contextualized way through simple commands; (iii) independent, that is, have a score equal to or greater than 43 points in the Preventive Medicine Exam for the Older People (in Spanish, EMPAM) of the Ministry of Health of Chile [24]; and (iv) complying with at least 85% attendance at the sessions scheduled for interventions. Regarding the exclusion criteria, the following will be considered: (i) having any disabling disease; (ii) those women who have musculoskeletal injuries or who are undergoing physical rehabilitation treatment that prevents their typical physical performance; and (iii) those who are permanently or temporarily unable to engage in physical activity. As depicted in Figure 1, all those who meet the inclusion criteria will be included in the study.

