### 2.6. Intervention

The TKD and MCT protocols will be distributed in three weekly sessions of 60 min on alternate days for 16-weeks (48 sessions). The general structure of the TKD and MCT protocols will include a 10 min warm-up consisting of joint mobility exercises and low-intensity aerobic work; then, for 40 min, the central part (TKD or MCT) will be developed to finish with a 10 min cool down through dynamic and static flexibility exercises. For their part, the WE protocol will be distributed in three weekly sessions of 45 to 60 min every other day for 16-weeks (48 sessions). A summary of the progression of all interventions is presented in Table 1.

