Following the above, proposing alternative physical activity strategies such as TKD programs for older people, especially for Chilean older women who have high rates of a sedentary lifestyle and overweight/obesity [18,19], can be a viable alternative for at least four reasons: (i) little space is required, which is consistent with the characteristics of Family Health Centers (in Spanish, CESFAM) and Community centers that host physical activity governmental workshops in Chile [22]; (ii) it requires tiny implementation because a large part of the activities are developed individually and in pairs [8,14]; (iii) low costs required to carry out this type of intervention, which would allow its use in a large population of older people [8]; and (iv) the variety of technical foundations that allow the use of innumerable combinations of movements, a fact that could generate greater motivation and adherence to training [8,14].

Among the possible limitations of the study protocol are: (i) difficulty recruiting older women who adhere to the study for 16-weeks plus the pre-intervention and post-intervention assessment periods; (ii) the impossibility of some participants to complete the sessions contemplated in the intervention due to the COVID-19 infection. Notwithstanding the above, our study will follow Chilean government guidelines for the safe return to the practice of physical activity in the context of the COVID-19 pandemic.

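### Adherence is offered as one advantage of taekwondo, but attendance is used only to select women and is not an outcome, so that part of the rationale goes untested

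*Protocol article*

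**What the plan says.** **Adherence as an argument.** The Introduction of the protocol article says of government-sponsored programmes: "However, their average adherence rate reaches 50"%. It gives a mean adherence above 80% for interventions based on Olympic combat sports and describes their other outcomes as similar to those of the usual strategies. It concludes that "taekwondo improves the health status of older people with adherence rates greater than 90% through interventions lasting 11 to 16 weeks". The Discussion gives at least four reasons for taekwondo. The fourth is technical variety, "a fact that could generate greater motivation and adherence to training".

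**Attendance in the methods.** It appears twice, each time as a selection rule:

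- Section 2.5 lists among the inclusion criteria "complying with at least 85% attendance at the sessions scheduled for interventions".
- Section 2.8.2 defines the per-protocol analysis: "Only those volunteers who have completed more than 85% of the training sessions will be considered for this analysis". It then applies the intention-to-treat procedures unchanged.

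**Outcome lists.** Section 2.7.1 lists health and fitness measures. Section 2.7.2, headed as secondary outcomes, holds only age, academic level and civil status. Section 2.8 describes no analysis of attendance. Section 2.6 schedules 48 sessions in each of the three training arms.

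**The concern.** The trial randomises women between taekwondo (TKD) and two of the usual strategies, multi-component training (MCT) and walking (WE), with the same number of sessions in each. It can therefore compare adherence without the confounding that affects rates taken from different studies and settings. The session count that both 85% rules require would supply the data, but the plan uses it only as a cut-off.

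Two things are at stake. First, a recommendation of taekwondo for public programmes could keep citing better adherence without randomised evidence for it. Second, attendance is observed after randomisation and may depend on the programme. If it does, the 85% cut keeps different fractions of the arms, and the women kept are no longer comparable by design. Section 2.8.2 carries no caution about this.

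**Working it through.** **1. Do the two thresholds differ?** With 48 sessions (section 2.6), 0.85 × 48 = 40.8. Attendance is a whole number, so the section 2.5 rule (at least 85%) and the section 2.8.2 rule (more than 85%) both mean 41 or more sessions. They pick the same women.

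**2. What happens if the section 2.5 rule is enforced?** Attendance cannot be known at enrolment. The rule could act only by removing women after randomisation. The intention-to-treat set in the training arms would then be the per-protocol set.

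**3. How much of an adherence difference would survive the cut?** Among women who pass, attendance runs from 41/48 = 85.4% to 100%. The largest possible difference between two arm means is 100 − 85.4 = 14.6 percentage points. The Introduction's figures suggest 90 − 50 = 40 points. A gap of that size could not be seen among the selected women.

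**4. What could 16 women per arm show if all were kept?** The 16 comes from section 2.3. The documents give no SD for attendance and do not define adherence rate, so both readings are shown.

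*Rates read as mean percentage of sessions attended.* Two-sample t-test, two-sided, 30 degrees of freedom, noncentrality (difference/SD) × √(16/2). SDs of 20 and 30 points are assumptions. The last column uses 0.05/3 for three pairwise comparisons, since section 2.8.1 adjusts post-hoc tests by Bonferroni.

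| Difference (points) | Assumed SD | Power, alpha 0.05 | Power, alpha 0.05/3 |
|---|---|---|---|
| 40 | 20 | >0.99 | >0.99 |
| 40 | 30 | 0.95 | 0.88 |
| 20 | 20 | 0.78 | 0.62 |
| 20 | 30 | 0.45 | 0.28 |
| 10 | 20 | 0.28 | 0.15 |

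On a 0 to 100 scale with mean 90, the SD cannot exceed √(90 × 10) = 30, so an SD of 30 is the extreme case for a taekwondo arm at that mean.

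*Rates read as proportions of adherent women.* For 50% against 90% with 16 per arm and two-sided alpha 0.05, power is 0.71 by the normal approximation and 0.58 by Fisher's exact test. For 50% against 80% it is 0.42 and 0.28.

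**5. Precision.** The 95% confidence interval for a difference in mean attendance has half-width 2.042 × SD × √(2/16). That is 14.4 points for SD 20 and 21.7 points for SD 30. Such an interval can speak to a gap of 40 points but not to one of 10.

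**The case against.** The strongest reply is that adherence is a background argument and the trial is about something else. Much of that stands. The Discussion puts space, equipment and cost first, and adherence is part of the fourth reason, worded as a possibility. The hypotheses concern cognition, brain activity, quality of life, postural balance and responder rates, all of which have a planned analysis. A reader might infer that adherence is the main reason for preferring taekwondo, or that the trial is unable to test its own rationale. The documents support neither. Only the adherence part goes untested, and only because of how the plan is written.

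A reader might also take the cited 50% and 90% as the gap to expect here, and conclude that the comparison would be well powered. That does not follow. The 50% belongs to government programmes, not to supervised MCT or WE in a trial that allows for 15% loss, and the power depends on an assumed SD and on how the rate is read.

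It can further be said that a condensed article may leave attendance summaries to the full protocol or analysis plan, that a per-protocol attendance cut is ordinary and sits beside an intention-to-treat analysis, and that recording of attendance is implied rather than stated. These are fair, and nothing here shows that attendance would go unreported. But the article does print its outcome lists and does fix attendance as a selection rule, including as an inclusion criterion. Those are statements, not gaps, and neither 85% rule can be applied without a session count.

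**Conclusion.** The point holds in a limited form. Adherence is put forward as one advantage of taekwondo, attendance serves only to select women, and the plan does not test that advantage. The per-protocol contrast between training arms rests on a post-randomisation selection that may differ by arm. How different is unknown, because the documents give no attendance figures for these arms.

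The attendance criterion in section 2.5 adds to this. If enforced, it would merge the two analysis sets in the training arms and cap any visible difference in mean attendance at 14.6 points.

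This is an inexpensive improvement worth making. No planned estimate of a health effect is shown to be wrong. The added comparison would reliably detect only a very large gap and should be read mainly through its confidence interval.

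**What to change.** 1. **Section 2.7.2:** add as secondary outcomes the number of sessions attended out of 48 and stopping training before week 16. Compare them across TKD, MCT and WE in all randomised women, count sessions after stopping as not attended, and report differences with confidence intervals. The control group has no sessions and does not enter.
2. **Section 2.5:** reconcile the attendance criterion with this comparison and with the intention-to-treat analysis in section 2.8.1, since attendance cannot be known at enrolment and enforcing it would truncate both.
3. **Section 2.8.2:** report the number in each training arm that meets the 85% cut, and state that the per-protocol contrast supports the intention-to-treat analysis and does not carry the conclusion alone.

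The cost is wording and a short analysis of counts that the 85% rules already require, with no new visits or participants. The downside is one more secondary comparison, with limited power for modest differences.

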## 3. Discussion

Despite being considered a risky activity [38], TKD has recently reported favorable physical, physiological, and psychoemotional responses in older people [9,15,16,17]. Previous studies have found that after 12-weeks of TKD and WE, participants had a considerably better response on static balance than a control group, with no differences between TKD and WE [39]. While one case study found that a TKD intervention reduced the chance of falls and the fear of falling in a 97-year-old man, the author adds that the evidence on the benefit proportionality of TKD in comparison to regularly used physiotherapy therapies is still unclear [40]. In this regard, conducting a study comparing the group and inter-individual responses (responders vs. non-responders) in older women subjected to a TKD program to other physical activity strategies adapted to the characteristics of older people (e.g., MCT and WE) could support the use of TKD as an efficient and safe activity for older women without putting their health at risk.

On the other hand, it is typical for interventions with young taekwondo practitioners to be of short duration (i.e., 4-weeks) using high-intensity interval training with specific techniques and an emphasis on improving physical performance [41,42,43,44]. These interventions cannot be extrapolated to older people, since the international physical activity recommendations suggest regular moderate to vigorous-intensity activities with emphasis on resistance training [3,5], which favors functional independence [4]. In addition, young taekwondo practitioners are generally athletes of regional or national level [41,42,43,44]. Therefore, the aim of the interventions does not seek to favor the health of the participants but rather the sports performance, instead, the older people generally practice physical activity to improve their health status [4,22].

Following the above, proposing alternative physical activity strategies such as TKD programs for older people, especially for Chilean older women who have high rates of a sedentary lifestyle and overweight/obesity [18,19], can be a viable alternative for at least four reasons: (i) little space is required, which is consistent with the characteristics of Family Health Centers (in Spanish, CESFAM) and Community centers that host physical activity governmental workshops in Chile [22]; (ii) it requires tiny implementation because a large part of the activities are developed individually and in pairs [8,14]; (iii) low costs required to carry out this type of intervention, which would allow its use in a large population of older people [8]; and (iv) the variety of technical foundations that allow the use of innumerable combinations of movements, a fact that could generate greater motivation and adherence to training [8,14].

Among the possible limitations of the study protocol are: (i) difficulty recruiting older women who adhere to the study for 16-weeks plus the pre-intervention and post-intervention assessment periods; (ii) the impossibility of some participants to complete the sessions contemplated in the intervention due to the COVID-19 infection. Notwithstanding the above, our study will follow Chilean government guidelines for the safe return to the practice of physical activity in the context of the COVID-19 pandemic.

## 4. Conclusions

This study protocol will analyze and compare the effects of a TKD program with respect to MCT and WE on health status in independent older women. Secondly, it will analyze the variability of the inter-individual response of the participants and compare them according to the designated training system. Our hypothesis indicates that TKD produces more significant effects and greater inter-individual responses (higher percentage of responders) in cognitive status, brain activity, health-related quality of life, and postural balance than MCT and WE. If this intervention proves to be beneficial, it might be included in public and private physical activity programs for older women.

## Figures and Tables

**Figure 1 biology-11-00816-f001:**
[figure not shown]
Study flowchart. Legends: CG: Control group (no intervention). MCT: multi-component training. *n*: number of participants. TKD: Adapted taekwondo. WE: Walking exercise.

**Figure 2 biology-11-00816-f002:**
[figure not shown]
Assessments and usual sessions of the intervention. Legends: CG: Control group. MCT: Multi-component training. TKD: Adapted taekwondo. WE: Walking exercise.

**Table 1 biology-11-00816-t001:** Progression for intervention (Training volume and intensity).

Program	Month	Weeks	Frequency (Weekly)	Total Time Per Session (min)	Exercise	Set	Rep	Rest	Intensity
TKD	1	1–4	3	60	UL	3	8	2 min	50–70% HRmax
					LL				
					Poomsae	---	6		
	2	5–8			UL	4	8		
					LL				
					Poomsae	---	6		
	3	9–12			UL	4	12		
					LL				
					Poomsae	---	6		
	4	13–16			UL	4	12	90 s	
					LL				
					Poomsae	---	6		
MCT	1	1–4		60	RT	3	10	2 min	OMNI-RES (5–8 points)
					CF				50–70% HRmax
					APC				
	2	5–8			RT	4	10		OMNI-RES (5–8 points)
					CF				50–70% HRmax
					APC				
	3	9–12			RT	4	12		OMNI-RES (5–8 points)
					CF				50–70% HRmax
					APC				
	4	13–16			RT			90 s	OMNI-RES (5–8 points)
					CF				50–70% HRmax
					APC				
WE	1	1–4		45	---	---	---	---	50–70% HRmax
	2	5–8		50	---	---	---	----	
	3	9–12		55	---	---	---	----	
	4	13–16		60	---	---	---	----	
Control group	1–4	16	Will be asked to maintain their usual activities of daily living.						

APC: Agility and postural control. CF: Cardiorespiratory fitness. HRmax: Maximum heart rate. LL: Lower limbs. MCT: Multi-component training. OMNI-RES: OMNI-Resistance Exercise Scale of perceived exertion. Poomsae: Sequence of arm and leg movements that simulate imaginary combat. Rep: Repetitions. RT: Resistance training. TKD: Adapted taekwondo. UL: Upper limbs. WE: Walking exercise.

## Data Availability

Not applicable.
